#### Power

Given the results identified using preliminary matching algorithms and chart review we assume that we will be able to identify 3 controls for 98% of LDs and at least one of those controls will be included in a more restrictive matched subset (i.e., known presence of CKD, known serum creatinine/urine protein at or prior to index date). For the following power analyses, the type-1 error probability is set to 5%.

For estimating the minimal detectible hazard ratio for all-cause mortality, we note that at present, 12% of UMN LDs, 7% of all Mayo LDs, and 11% of identified preliminary controls are deceased. With a mortality rate of 11% in our study population, we estimate that our minimal detectible hazard ratio with 80% power will be 1.13 for a 3:1 matching and 1.16 for a 1:1 matching.

In UMN LDs, approximately 13.5% have developed eGFR < 45 ml/min/1.73m^2^ during follow-up. In our analysis comparing the risk of developing an eGFR < 45 between UMN LDs and healthy controls, we conservatively estimate that eGFR < 45 will develop in approximately 8 to 14% of our study population. With this assumption, our minimal detectable hazard ratio will be between 1.20 and 1.15 for a 3:1 matching and between 1.25 and 1.18 for a 1:1 matching.

Among the 301 UMN LDs who developed DM after donation without first developing CVD, 57 individuals (19%) later developed CVD. Assuming identification of a 1:1 match for approximately 80% (240) of these donors and that the overall proportion of individuals in our study population who develop CVD after DM ranges from 15 to 23%, we will have 80% power to detect a hazard ratio between 1.94 and 1.70.

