#### Statistical analyses details

Log-rank tests and Kaplan Meier curves will be used as preliminary assessments to compare the risk of all-cause mortality and cardiovascular mortality, CVD, ESKD, CKD (eGFR < 45; eGFR < 30 ml/min/1.73m^2^), proteinuria, DM, and hypertension after index date between LDs and healthy controls. Our study is powered based on these analyses. Cox proportional hazards models will also be used to test for an increased risk of adverse outcomes in living LDs versus controls while directly accounting for the variables used for matching (to account for any possible residual imbalance between the cohorts similar to how one may adjust for characteristics in a randomized controlled trial to account for residual imbalance and to improve efficiency). In analyses involving Mayo LDs and their associated controls we will account for donation center (Mayo vs. UMN) as a covariate in the model. If the proportional hazards assumption fails, an alternative method such as an accelerated failure time model will be considered. Indeed, the risk of mortality and ESKD may disproportionately increase with long-term follow-up on the 60-year scale of this study [123, 130, 131]. A similar approach will be used to test for increased risk of outcomes for LDs versus controls after development of DM, hypertension, proteinuria, de novo kidney disease, or pregnancies with gestational hypertension or preeclampsia, but additional measures (e.g. matching, adjustment) will be used to account for the time of disease onset.

In order to evaluate biases in the selection of controls and ascertain outcomes, we will compare the risk of non-kidney-related cancer between donors and controls using the previously described methods. As cancer risk is lower in donors than the general population, we expect a similar lower risk in controls [150]. If controls are well matched, we do not expect the risk of non-kidney related cancer to differ between donors and controls. If a difference in cancer risk is identified, it may indicate imbalance in our matching and it will be further investigated using methods described in Shi et al. [151].

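### Power for CVD after diabetes: the favourable end (HR 1.70 at 23% overall) does not fit the donors' own printed rate of 19%, which supports a detectable HR of about 1.95

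*Protocol article*

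**What the plan says.** The section on statistical analysis details names log-rank comparisons of donors with controls and says "Our study is powered based on these analyses". The Power section fixes the error rate ("For the following power analyses, the type-1 error probability is set to 5"%), without stating whether it is one- or two-sided.

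- **CVD after DM.** The donor experience so far is: "Among the 301 UMN LDs who developed DM after donation without first developing CVD, 57 individuals (19%) later developed CVD". A 1:1 match is assumed for about 80% of these donors (240). The plan then takes it that "the overall proportion of individuals in our study population who develop CVD after DM ranges from 15 to 23%, we will have 80% power", and gives the result as "we will have 80% power to detect a hazard ratio between 1.94 and 1.70".
- **eGFR below 45.** Among University of Minnesota donors, "approximately 13.5% have developed eGFR < 45 ml/min/1.73m"². For donors and controls together, "we conservatively estimate that eGFR < 45 will develop in approximately 8 to 14% of our study population". The detectable hazard ratios are printed as 1.20 to 1.15 (3:1) and 1.25 to 1.18 (1:1).

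The Aims and hypotheses section expects donors to have slightly higher incidence than controls, so the alternative of interest is a hazard ratio above 1.

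**The concern.** The assumed proportions are for donors and controls combined. If donors have the higher risk and both groups are followed equally long, the combined proportion must lie between the control and donor proportions, and therefore below the donor one. The 15 to 23% range is the donors' 19% plus or minus 4 points, so its upper half lies above the donor rate. The text does not say how the range was chosen.

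The number of events drives the detectable hazard ratio, so a combined rate that is too high makes the study look more sensitive than its own inputs allow. This is the only power statement for outcomes after a new comorbidity, a comparison that the Discussion presents as a strength of the study. A null result could be read as excluding a hazard ratio of 1.70 with 80% power when the power was nearer 60%.

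**Working it through.** **Inputs (Power section unless noted).** CVD after DM: 240 donors, 1:1, 480 people; donor proportion 57/301 = 18.9%; combined proportion 15% and 23%. eGFR below 45: 4022 donors (section on the UMN LD cohort) × 0.98 = 3,942; donor proportion 13.5%; combined proportion 8% and 14%. Two-sided 5% is my assumption. It is the reading that reproduces the printed figures; one-sided gives 1.80 and 1.61 for CVD.

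**Step 1: reproduce the printed figures.** Schoenfeld formula, with a the donor share of the sample:

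HR = exp[(1.960 + 0.842) / √(events × a × (1 − a))], events = total N × combined proportion.

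| Analysis | Combined rate | Events | HR computed | HR printed |
|---|---|---|---|---|
| CVD after DM, 1:1 | 15% | 72 | 1.936 | 1.94 |
| CVD after DM, 1:1 | 23% | 110.4 | 1.705 | 1.70 |
| eGFR < 45, 3:1 | 8% | 1,261 | 1.200 | 1.20 |
| eGFR < 45, 3:1 | 14% | 2,207 | 1.148 | 1.15 |
| eGFR < 45, 1:1 | 8% | 631 | 1.250 | 1.25 |
| eGFR < 45, 1:1 | 14% | 1,104 | 1.184 | 1.18 |

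The formula was applied correctly. The question is the rate put into it.

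**Step 2: control rate implied by the upper ends.**

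- CVD after DM, 1:1: 2 × 23% − 19% = 27%. The implied hazard ratio is ln(1 − 0.19) / ln(1 − 0.27) = 0.67.
- eGFR < 45, 1:1: 2 × 14% − 13.5% = 14.5%.
- eGFR < 45, 3:1: (4 × 14% − 13.5%) / 3 = 14.2%.

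In all three the controls exceed the donors.

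**Step 3: make the rates consistent.** Hold the donor proportion at its printed value and set

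control proportion = 1 − (1 − donor proportion)^(1/HR).

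CVD after DM at HR 1.70:

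- Controls: 1 − (1 − 0.189)^(1/1.70) = 11.6%.
- Combined: 15.3%, so events = 480 × 0.153 ≈ 73, against 110 assumed.
- Power: Φ(ln 1.70 × √(73.3 × 0.25) − 1.960) = Φ(0.31) ≈ 62%. A log-rank simulation of 4,000 runs with donors at 19% gave 61%.
- Solving for 80% power gives HR ≈ 1.95 (controls 10.2%, about 70 events).

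eGFR < 45 with donors at 13.5%:

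- 3:1: power at 1.15 is 76%; detectable HR about 1.16.
- 1:1: power at 1.18 is 74%; detectable HR about 1.20.

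**Step 4: could later follow-up rescue HR 1.70?** The same calculation with higher donor proportions for CVD after DM:

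| Donor rate | Power at HR 1.70 | Detectable HR |
|---|---|---|
| 19% | 62% | 1.95 |
| 23% | 71% | 1.82 |
| 25% | 74% | 1.77 |
| 28% | 79% | 1.71 |

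A combined 23% together with HR 1.70 needs donors at 28.3% and controls at 17.7%. For eGFR < 45, a combined 14% needs donors at 15.4% (3:1, HR 1.15) or 15.1% (1:1, HR 1.18).

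**Step 5: the unfavourable ends.** With donors at the printed rates, power is about 79% at HR 1.94 for CVD, and about 93% at 1.20 (3:1) and 1.25 (1:1) for eGFR < 45.

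**The case against.** The best defence is that the ranges are openly labelled as assumptions, both ends are printed, and the value I call consistent (1.95) is in effect the printed 1.94. The donor proportions are also rates to date. The new survey and continuing donor contact will add events, so the final donor proportion can exceed 19%. The check further assumes proportional hazards, equal follow-up after DM onset, and that the 240 matched donors share the rate of all 301; the article confirms none of these. Finally, the donor cohort is fixed, so no sample size depends on these figures.

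Most of that stands as a limit on the claim. The shortfall is conditional on the donor rate, and the range does contain nearly the right answer at one end. It does not rescue the other end: the Power section states no projection, and growth to 23% in the donors themselves would still leave 71% power at 1.70. A relative rise of about half, to 28%, is needed.

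Three stronger readings are tempting and are not supported:

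- **That the power formula was misapplied.** Every printed hazard ratio follows from its stated input.
- **That the eGFR figures are equally at fault.** There the gap is half a point between two approximate figures, and it moves the hazard ratio by 0.01 to 0.02. Part of the 1:1 shortfall is rounding: 1.184 was printed as 1.18, which has only 78.5% power even at 14%. Donors at about 15% would support the printed values.
- **That the plan calls the 14% end conservative.** The word describes the whole 8 to 14% range, most of which lies below the donor rate.

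**Conclusion.** The favourable end of the CVD-after-DM statement is inconsistent with the donor rate printed beside it. At the observed 19%, with proportional hazards and equal follow-up in both groups, power at HR 1.70 is about 62% and the hazard ratio detectable with 80% power is about 1.95. The part of the printed range well below 1.94 rests on a rise in the donor rate that the article does not state. The eGFR < 45 statement has the same inconsistency at a size that barely matters (about 1.16 and 1.20, inside the printed ranges). The unfavourable ends 1.94, 1.20 and 1.25 stand. The point affects how a null result after DM should be read; it does not affect how the study is run.

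**What to change.** In the Power section, state donor and control proportions separately and derive the combined rate from the donor rate and the hazard ratio tested, using control proportion = 1 − (1 − donor proportion)^(1/HR).

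- **CVD after DM:** report about 1.95 at the observed 19%. If further follow-up is expected to raise the donor rate, state the rate assumed and the hazard ratio that goes with it: about 1.82 at 23%; about 1.70 only with donors near 28%.
- **eGFR < 45:** give about 1.16 (3:1) and 1.20 (1:1) at 13.5%, or state that donors are expected to reach about 15%.
- State that the 5% level is two-sided, if it is.

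The cost is a few reworded sentences and a less favourable CVD figure. Matching, data collection and analysis do not change.

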## Discussion

The MARKD study will evaluate the attributable long-term risk of kidney donation by matching LDs from two transplant centers with controls from a large, contemporaneous, geographically similar epidemiological cohort. A similar study with the number of LDs and healthy matched controls and length of detailed follow-up could not be done anywhere else worldwide. While our geographic location is constrained in terms of ethnic/racial diversity, no other transplant centers have detailed long-term donor follow-up with a truly well-matched control group. The Norwegian study described previously has the longest healthy matched-control study to date [55]. However, it has a much smaller sample size and numerous limitations as previously described [103–115]. In the US, the OPTN did not start collecting Social Security numbers of donors until 1994, limiting linkages to other databases to obtain information on ESKD and mortality. Also, before 1996, LDs with ESKD listed with the OPTN for a transplant were not necessarily identified as a LD [152]. And today, even 6-month follow-up in the OPTN database remains poor [152–155].

The MARKD study will focus on LDs in two LD programs that started in 1963, and REP-controls dating back to 1963 with comprehensive medical records that are ongoing. A unique aspect of our study is the granular long-term follow-up. The UMN LD program has surveyed LDs every 3 years. The REP links the full life course medical records of nearly all Olmsted County providers, allowing electronic (ICD-9/10 codes) and manual (chart abstraction) review of the comprehensive medical record of controls. No other study of this size provides: (a) this length of follow-up (more than three decades longer follow-up than the US OPTN registry), and (b) detailed ongoing follow-up of LDs and healthy-matched cohorts. Developing a matched control cohort from the REP will not only allow us to provide the best and the longest data on long-term LD outcomes to date, but will also lay the groundwork for future analyses.

A major innovative aspect of our study is our contemporaneous healthy matched control cohort. Unlike prior studies, we will more clearly delineate matched controls that reflect the health status of donors just prior to the date of donation. This will be accomplished by identifying controls known to be healthy and with normal renal function at the index date (matched to donation date) who are from the same geographical region of residence (Upper Midwest) as donors, and by obtaining granular data on controls to allow for optimal matching of controls to LDs on key characteristics (including family history of CKD).

Longitudinal follow-up of both LDs and REP controls provides detailed, uniquely available health information on events preceding ESKD and mortality. In contrast to previous studies, we will compare LDs and healthy-matched REP controls on the much more common intermediate endpoints (e.g., low GFR; CVD) that occur before ESKD or death. Additionally, we will be able to study outcomes of LDs who develop new comorbidities late after donation (e.g., obesity, hypertension, DM, early or late GFR < 45 ml/min/1.73m^2^, proteinuria). This will provide information about whether the impact of these comorbidities differs for those with 1 vs. 2 kidneys. That is, we will be able to assess if differences in long-term outcomes between donors and controls are mediated by differences in postdonation comorbidities.

We will be among the first studies to evaluate modifiers of the effect of donation on ESKD and mortality. There have been several studies of risk factors for developing ESKD in the donor population. However, these identified risk factors are also risk factors for ESKD in the general population. By using well-matched REP controls, we will be able to assess the effect of donation for “ideal” LDs and for LDs who, at donation, have risk factors for CKD. That is, ours will be among the first studies to test if the attributable risk of an outcome with kidney donation is modified by clinical and demographic factors (e.g., age, BMI, smoking, donation eGFR).

Another strength of our study is uniform event ascertainment. Use of national databases (NDI, USRDS), access to long-term historical data, and a new survey sent at the same time to LDs and controls will allow us to ascertain events by the same approach in both LDs and controls. Simultaneously obtaining outcomes for both groups the same way will avoid a differential ascertainment bias. Further, the granular long-term follow-up of REP controls and the UMN LD program will provide independent sources for validating the timing and onset of self-reported outcomes on the new survey. Thus, we will be able to provide the most complete and detailed information on long-term LD outcomes as compared to a well-matched healthy control cohort.

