### Study cohorts

#### UMN LD cohort

From January 1, 1963 through December 31, 2012, there were 4022 LDs at UMN who met the study criteria. Most LDs were from the upper Midwest region of the US, and detailed descriptions of the UMN LD cohort have been published [45, 50]. At donation, laboratory and demographic variables, surgical information, and peri-operative course information is collected. Prior to 2003, LDs were surveyed intermittently. In 2003, all donors were contacted to be surveyed and asked to consent to be surveyed every three years. Since 2003, consenting LDs are surveyed postdonation at regular intervals (6, 12, and 24 months, and then every 3 years). Those not returning to the clinic are sent a survey (by mail; or, if preferred, by email) to determine health status. If the survey is not returned, the LD is contacted by phone monthly, for 3 months. At least one phone call is made in the evening and one on weekends to increase response rates. LDs are also asked to provide alternate contacts. For LDs who become lost to follow-up UMN uses these contacts to ask for a current phone number and address. Available internet search engines and other databases (e.g., Accurint.com, Peoplefinder.com) are also used to identify LDs lost to follow-up.

At each contact, LDs are asked about hypertension, DM, and other diagnoses requiring treatment. Female donors are asked about pregnancy history. LDs are also asked to provide recent lab test results and copies of medical records; alternatively, with LDs’ permission, UMN investigators contact local clinics for recent medical records that include clinical notes and laboratory test results, including serum creatinine, glucose, urinalysis, and urinary protein measurements. Those without recent information are asked to get a history, physical, and labs at their local physician’s office and have the results sent to UMN. For LDs willing to do the tests but without insurance coverage, UMN pays for them. A summary of the clinical and demographic characteristics of the UMN LD cohort is given in Table 1.

**Table 1 Tab1:** Characteristics of the University of Minnesota (UMN) and Mayo Clinic donors

	UMN donors (N = 4022)	Mayo donors (N = 3035)
Years from donation to last survey or History & Physical (mean ± SD)	22.04 ± 11.93	
No returned surveys	9.5%	
Sex (%)		
Female	2294 (57.0%)	1668 (55.0%)
Male	1728 (43.0%)	1354 (44.6%)
Unknown	0 (0%)	13 (0.4%)
Age at donation (mean ± SD)	39.02 ± 11.64	42.52 ± 11.98

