### Outcomes

Outcomes include mortality, CVD and cardiovascular mortality, serial creatinine (to determine eGFR trajectory and chronic kidney disease) and other laboratory measures, pregnancy outcomes and complications, and development of diseases that frequently lead to CKD (e.g., hypertension, DM, and obesity). Outcomes will be ascertained from national registries, medical record review of donors and REP controls, and a new survey administered to both donors and controls. A list of data collected, data source, and frequency of data collection is provided in Table 2 and is summarized below.

**Table 2 Tab2:** Data collection sources and frequency for REP controls and UMN donors. CR: Chart Review, DS: Donor survey + chart review if available (every 3 years), SS: Study Survey, LD: Lab data (every year)

	Source of data	
Data	UMN Donors	REP Controls

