**Baseline characteristics**		
Demographics	CR	CR^1^
History of substance abuse^2^	CR	CR
Diagnosis of Depression/Anxiety Disorder^3^	CR	CR
High cholesterol	CR, SS	CR, SS
Hypertension^4^	CR, SS	CR, SS
Family history of kidney disease, DM, HTN	CR, DS, SS	CR, SS
Smoking history	CR, DS, SS	CR, SS
**Lab measurements**	Requested every 3 years with study survey	Recorded every year if available
BUN/Urea	CR	CR, LD
Glucose	CR	CR, LD
Urine protein^5^	CR	CR, LD
BMI	CR, DS, SS	CR, LD, SS
Creatinine	CR, DS, SS	CR, LD, SS
Blood pressure	CR, DS, SS	CR, LD, SS

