**Outcomes**		
CVD^6^	DS, SS	CR, SS
Diabetes	DS, SS	CR, SS
Cancer	DS, SS	CR, SS
Hematuria	DS, SS	CR, SS
High cholesterol treated with medication	DS, SS	CR, SS
Hypertension treated with medication	DS, SS	CR, SS
Pregnancy history^7^	DS, SS	CR, SS
Proteinuria	DS, SS	SS
Kidney disease/ abnormal kidney function/ ESKD	DS, SS, USRDS	CR, SS, USRDS
Vital status and cause of death	DS, SS, NDI	CR^8^, SS, NDI

^1^ Chart review for controls includes abstraction of data from electronic transfer from the Rochester Epidemiology Project (REP) database, Mayo clinic paper records, Olmstead Medical Center electronic and paper record, Olmstead Community Hospital electronic and paper records, Epic, and the REP browser (electronic record system) from date of first REP encounter to date of last follow-up

^2^Permissible substance abuse at donation/donation is defined as a remote history of marijuana use with no active use around the time of the donation date or current marijuana use as long as it does not interfere with lifestyle. Remote other substance use is not a contraindication to donation as long as its truly remote

^3^Permissible depression/anxiety at donation/donation is defined as well controlled, in the distant past prior to the donation date, or involving few episodes of care

^4^Permissable hypertension at donation/donation includes that which is well controlled (< 140/90), treated with a diuretic antihypetensive agent, a non-diuretic antihypertensive agent, or both (1 diuretic and 1 non-diuretic hypertensive agent), age needs to be > 50 years. Exclude if age < 50 years or not well controlled or using 2 or more non-diuretic agents or using 2 or more diuretic agents

^5^Urine Dipstick, 24 H Urine Protein, Urinalysis Predicted 24-Hour Protein, Protein-Osmolality Ratio, Urine Protein to Creatinine Ratio, Urine Albumin to Creatine Ratio, 24 H Urine Albumin

^6^Congestive heart disease, myocardial infarction, cerebrovascular accident, transient ischemic attack, angioplasty, stents

^7^Number and year of pregnancies, pregnancy outcome (singleton, twins, triplets, ≥ 4, abortion, miscarriage, fetal death), gestational length (full term, pre-term), and pregnancy complications (gestational hypertension, gestational diabetes, proteinuria, eclampsia, preeclampsia)

^8^Proof of life noted for medical encounters with no data

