#### Survey data: mortality, ESKD, and other outcomes

UMN donors and validated REP controls not known to be deceased will be sent a standardized survey to determine outcomes. This survey is based on the existing survey that has been used for UMN donors, but modified to be usable with both LDs and controls. This survey supplements the capture of key data that may not be consistently documented in the medical record with specific items including: hematuria or proteinuria of at least 6 months duration, hypertension, DM, heart failure, myocardial infarction, angioplasty or stent, angina, smoking history, and pregnancy history; and family history of hypertension, DM, or ESKD (see **Supplemental Materials** for the survey). We will additionally capture cancer information to use as a negative control (see statistical analysis section).

The survey will allow for uniform ascertainment of outcomes between UMN donors and REP controls. Because Mayo LDs have not been routinely contacted about health outcomes after donation, they do not have a similar long-term follow-up history as UMN LDs from which to validate survey responses. Because of this and budgetary constraints, only the REP controls and UMN donors will be surveyed.

UMN donors will be contacted to complete the survey using a similar process as described previously for the 3-year postdonation follow-up surveys. Data obtained from this new survey will be used to supplement data collected in the triannual surveys sent to UMN donors previously.

For REP controls, mailing addresses and phone numbers will be obtained from recent Olmsted County medical care episodes. REP controls without a recent medical visit will be queried in Accurint™ to determine if they are alive and if so, identify their most recent mailing address and phone number. Up to three mailed surveys, with the first including an incentive item for participation, will be sent to the controls followed by up to 5 phone calls (including evenings and weekends). After surveying the first validated control for each REP donors, we will prioritize surveying controls for donors who lack completed surveys by a matched control.

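### Event ascertainment is called uniform, but Table 2 gives donors and controls different sources and schedules for most non-registry outcomes, and its two entries for control proteinuria disagree

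*Protocol article*

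**What the plan says.** The Discussion presents uniform ascertainment as a strength. The national registries, historical data and a new survey "will allow us to ascertain events by the same approach in both LDs and controls", and "Simultaneously obtaining outcomes for both groups the same way will avoid a differential ascertainment bias".

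Table 2 defines the sources. For donors, "DS: Donor survey + chart review if available (every 3 years"); for controls, chart review (CR) and "LD: Lab data (every year"). Both groups get the new study survey (SS). Donor laboratory values are requested every 3 years with the survey; control values are "Recorded every year if available". Under UMN LD cohort, regular 3-yearly contact dates from 2003: "Prior to 2003, LDs were surveyed intermittently".

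The survey section limits the new survey to UMN donors and validated controls not known to be dead. It also sets an order of priority for surveying controls and leaves Mayo donors out. Statistical analyses details plans non-kidney cancer as a negative control for bias in selection and ascertainment.

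**The concern.** If events are found by different routes in the two groups, part of any donor-control difference may reflect how hard each group was looked at. The article holds others to this standard. Limitations of prior work faults the earlier US study because its ESKD definition differed between donors and non-donors. Primary control group and matching algorithms treats selective testing at baseline as a detection-bias problem and builds several control cohorts to bound it. For follow-up the article describes no such bounding, and the Discussion declares the problem avoided.

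The planned negative control does not fill the gap. Cancer is itself taken from donor survey plus new survey in donors and from chart review plus new survey in controls. A cancer difference could therefore come from poor matching or from unequal capture, and offsetting biases could hide each other. Nor does cancer test laboratory-schedule bias. The results matter beyond the paper, because Dissemination plans a public risk calculator that includes intermediate outcomes.

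**Working it through.** **Step 1: sources side by side (Table 2).**

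| Item | UMN donors | REP controls | Shared source |
|---|---|---|---|
| CVD, diabetes, cancer, hematuria, treated cholesterol, treated hypertension, pregnancy | DS, SS | CR, SS | SS |
| Proteinuria (outcome row) | DS, SS | SS | SS |
| Urine protein (laboratory row) | CR | CR, LD | CR |
| Creatinine | CR, DS, SS | CR, LD, SS | CR, SS |
| Kidney disease/ESKD | DS, SS, USRDS | CR, SS, USRDS | SS, USRDS |
| Vital status, cause of death | DS, SS, NDI | CR, SS, NDI | SS, NDI |

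Only NDI, USRDS and the new survey are obtained the same way in both groups. CR and DS are the historical data, and they differ. The new survey cannot equalise the groups, because it reaches only people not known to be dead and is pooled with the unequal sources.

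**Step 2: proteinuria.** The outcome row gives controls SS only. The laboratory row gives them CR and LD, and the medical record review section lists urine protein among the control measures abstracted up to once per calendar year after index. The two rows cannot both describe the outcome. The survey item concerns proteinuria lasting at least 6 months, which is also not a laboratory definition. Under a literal reading of the outcome row, a control who died before the survey or did not respond contributes no event. The Power section puts 11% of preliminary controls as deceased; the response rate is not given.

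**Step 3: reproduce the plan's sensitivity.** The Power section gives detectable hazard ratios for eGFR < 45 in UMN donors. Inputs: 4,022 donors, 98% matched, k controls per donor, 8% or 14% with events, 5% type-1 error (two-sided), 80% power.

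HR = exp[(1.960 + 0.842)/√(D·p·(1−p))], with D = 4,022 × 0.98 × (1 + k) × event proportion and p = 1/(1 + k).

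| Matching | Events, 8% / 14% | HR computed | HR stated |
|---|---|---|---|
| 3:1 | 1,261 / 2,207 | 1.200 / 1.148 | 1.20 / 1.15 |
| 1:1 | 631 / 1,104 | 1.250 / 1.184 | 1.25 / 1.18 |

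All four figures reproduce.

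**Step 4: what unequal detection alone could do.** Assume a true HR of 1 and an apparent HR equal to the donor/control detection ratio r (rare-event approximation). The values of r are assumptions. The probability of a significant result is approximately Φ(ln r·√(D·p·(1−p)) − 1.960). At 3:1:

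| r | 8% events | 14% events |
|---|---|---|
| 1.05 | 0.11 | 0.17 |
| 1.10 | 0.31 | 0.49 |
| 1.15 | 0.58 | 0.81 |
| 1.20 | 0.80 | 0.96 |

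For r = 1.15 and 8% events: 0.1398 × 15.38 − 1.960 = 0.19, and Φ(0.19) = 0.58.

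**Step 5: direction.** A simulation gave both groups the same eGFR process over 22 years (assumed: baseline mean 85, SD 12; slope mean −0.8 per year, SD 0.6), with testing independent of health. Donors were tested 3-yearly and controls yearly, at assumed uptakes. Apparent HR = ln(1 − d)/ln(1 − c), where d and c are the proportions detected in donors and controls.

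| Donor / control uptake | No measurement noise | Noise SD 6 |
|---|---|---|
| 100% / 100% | 0.87 | 0.68 |
| 90% / 70% | 0.86 | 0.73 |
| 90% / 50% | 0.96 | 0.83 |
| 60% / 70% | 0.73 | 0.57 |
| 90% / 33% | 1.07 | 1.01 |

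The true HR is 1 throughout. The apparent HR falls on either side of 1, depending on testing rates that the article does not give.

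**The case against.** The strongest reply is that this is one over-broad Discussion sentence and one inconsistent table row, with harmonisation rules left to a fuller document. Much of that stands on size, but the claim and the table that contradicts it are both in this article. Several stronger readings also fail.

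- **Donors under-report, so harm is masked.** A reader might infer this from survey against chart. But DS includes chart review where available, UMN abstracts its own and affiliated records, seeks local records with permission, and pays for tests in willing donors without coverage. Control follow-up in charts is passive. No direction is established.
- **Early donors are poorly captured.** By index decade, 99 + 658 + 796 + 1,040 = 2,593 of 4,022 UMN donors (64.5%) donated before 2000. They are not lost: all donors were contacted in 2003, only 9.5% returned no survey, and mean time to last survey or examination is 22 years.
- **Proteinuria will show a large spurious excess in donors.** With 89% of controls alive and an assumed 50–70% responding, control capture would be 0.445–0.623; against an assumed 90% in donors the ratio is 2.0–1.4. That holds only if the abstracted urine-protein results go unused, which the laboratory row and the medical record review section make doubtful.
- **The survey omits stroke and TIA.** Table 2 defines CVD as "Congestive heart disease, myocardial infarction, cerebrovascular accident, transient ischemic attack, angioplasty, stents", while the survey section lists "heart failure, myocardial infarction, angioplasty or stent, angina, smoking history, and pregnancy history". That list is introduced as examples and the instrument is in a supplement not shown, so an omission cannot be concluded.
- **All non-fatal outcomes are affected alike.** ESKD has USRDS in both groups, as death has NDI; only their supplementary sources differ.

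The cancer negative control is a real, though partial, check and should stay.

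**Conclusion.** The uniformity claim is wrong as worded. It holds for NDI, USRDS and the new survey, the last only for UMN donors and controls not known to be dead. For the other non-registry outcomes the historical sources differ, and for eGFR and other laboratory measures the schedules differ. Those comparisons are at risk of differential ascertainment; the article does not show that bias will occur, in which direction, or how large it would be.

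The firmest defect is internal: the proteinuria outcome row and the control urine-protein collection disagree, and the outcome row taken literally removes non-responders and the dead from the control events.

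The 0.58 to 0.81 false-positive probability rests on an assumed 15% detection difference and applies to eGFR < 45 at 3:1 matching. It should not be carried over to CVD or diabetes: the only CVD figure in the Power section, CVD after diabetes, has a detectable hazard ratio of 1.70 to 1.94.

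**What to change.** 1. **Proteinuria.** Reconcile the Table 2 rows by adding the controls' chart and yearly urine-protein results to the outcome, with one laboratory definition in both groups.
2. **CVD, diabetes, hypertension, cancer.** Report a new-survey-only comparison as a sensitivity analysis beside the pooled-source one, stating that it covers only surviving responders. Do not make a reported donor effect depend on agreement between the two, since real harm could then go unreported. For eGFR thresholds, add a sensitivity analysis on a common measurement grid. It should not be the main analysis, because thinning control values does not cure missing or indication-driven testing.
3. **Death and ESKD.** Report NDI-only and USRDS-only results as same-source sensitivity analyses. Keep the supplementary sources in the main analysis, as the article does not state which years the registries cover.
4. **Negative control.** Keep non-kidney cancer as planned and add NDI non-kidney cancer death beside it. A difference in both points towards matching; a difference only in reported cancer points towards unequal capture. The NDI version also covers Mayo donors.
5. **Wording.** Limit the uniformity statement in the Discussion to NDI, USRDS and the new survey.

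The cost is outcome-definition wording and a set of extra analyses on data already planned. The survey-only version is restricted to survivors who respond, so it informs the main result without replacing it.
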